### Assessment of chemosensitivity of fresh parasite isolates

The remaining pellet from the 2 ml sample taken for clinical chemistry (following centrifugation and removal of the plasma for the clinical chemistry tests) will be used for the *in vitro* tests. Subsequently, the leukocytes will be also be removed. After washing the cells for 3 times with 2 V of complete RPMI medium containing AB serum will be added to the red blood cells and centrifuge at 2000 rpm for 5 min. After removing the supernatant, this step will be repeated 2 more times. The resulting pellet will be re-suspended in a 1 V RPMI medium and a thin film will be made to check the parasitaemia. If the parasitaemia is >0.5 %, flesh erythrocytes will be added to bring down the parasitaemia to 0,5%. The haematocrit will be adjusted to 5% with RPMI. A volume of 200 μl of this suspension will be added into each well of the 96-well plate containing 50 μl of the drug solution (in RMPI), at ascending concentrations of drugs. The plate will be incubated for 48 hours at 37 ºC. Thereafter, radiolabelled hypoxanthine-(H3) will be added and the plates incubated for another 18 hours before assessing the parasite growth by radioactivity counting.

### Determination of the plasma concentration of piperquine at asexual breakthrough infections during follow-up

Breakthrough infections (recrudescent or new infections) from patients treated with dihydroartemisinin-piperaquine will be characterized in terms of piperaquine plasma levels at time of asexual parasite reappearance to analyse the relationship of drug selection pressure and the emergence of parasite resistance to piperaquine. The analysis will include (1) samples obtained from patients with subsequent asexual parasite reappearance due to recrudescence or reinfection and (2) a corresponding number of random samples obtained from patients without such an event during follow-up (total number of patients with breakthrough infections is estimated at approx. 50). These pharmacokinetic analyses will be performed in collaboration with [name], KEMRI/Wellcome Trust Research Programme Nairobi and [name], Mahidol University Bangkok, Thailand.

### Detection of sub-patent asexual parasitaemia on days 7 and 14 to predict subsequent parasitological failure

Samples collected for day 7 haematology **and day 14** will be stored at -80ºC. Total RNA will be extracted (1) from samples obtained from patients with subsequent asexual parasite reappearance due to recrudescence or reinfection and (2) from a corresponding number of random samples obtained from patients without such an event during follow-up (total number of patients with breakthrough infections is estimated at approx. 50). The sensitivity of the subsequent analytical step will be increased by unspecifically amplifying extracted total RNA. Reverse transcriptase−polymerase chain reaction (RT-PCR) will then be used to detect transcripts of the ring-infected erythrocyte surface antigen, which exhibits asexual stage-specific expression. These investigations will be conducted in collaboration with the University of Heidelberg, Germany.

### Investigation of the relationship between *var* gene transcription patterns and late asexual parasite recurrence

**RNA will be collected in Roche RNA/DNA Stabilization Reagent for Blood/Bone Marrow. mRNA will be extracted using Roche mRNA Isolation Kit for Blood/Bone Marrow. The RNA analysis method follows previously described protocols (Bull et al., 2005; Kyes et al., 2000). Briefly, cDNA will be prepared from DNA-depleted total RNA DBLα sequences will be amplified using a primer annealing to the semi-conserved 5’ and 3’ ends of DBLα regions. Following PCR, purified DBLα sequences will be ligated into an appropriate vector and used to transform TOP10 cells. From each clinical isolate we aim to sequence approximately 50 cDNA DBLα clones. Sequencing will be carried out using an Applied Biosystems sequencing system. The expression patterns of *var* genes between pairs of isolates from baseline and asexual parasite recurrence will be examined for switches in dominant *var* gene transcripts. The equipment for the required high throughput sequencing is currently not yet available in Kenya and samples will therefore be analysed by the collaborating institution in the United Kingdom (Wellcome Trust Sanger Institute, Cambridge, UK). Samples will be stored at -80ºC until analysis. Storage of samples beyond the analysis stage is not planned.**

## Patient follow-up

Patients will be monitored daily until parasite and fever clearance is achieved. Active follow-up will be on days 3 and 7, then weekly on days 14, 21, 28, 35, 42, 56, and 63 and finally again on day 84; all subjects will be seen on any day between 0 and 84 upon request. The patient-specific CRF will be used to record clinical and laboratory data on each on these visits.

## Safety assessment and reporting of symptoms and serious adverse events

Safety and tolerability of the treatments will be evaluated by recording Adverse Events (AEs) and grading, laboratory, ECG and vital signs evaluations.

### Adverse Events

At each visit, the Investigator will ascertain the occurrence of any adverse events since the last visit. Any event must be recorded on the CRF.

#### Definition of an Adverse Event

An AE is any untoward medical occurrence in a patient or clinical investigation subject administered a pharmaceutical product and which does not necessarily have a causal relationship with this treatment.

An AE can therefore be any unfavourable and unintended sign (that could include a clinically significant abnormal laboratory finding), symptom or disease temporally associated with the use of a medicinal product, whether or not considered related to the medicinal product.

#### Severity, Relationship of Event to Study Drug, and outcome

The severity of an adverse event is to be scored according to the following scale:

1. Mild Awareness of sign or symptom, but easily tolerated
2. Moderate Discomfort enough to cause interference with usual activity
3. Severe Incapacitating with inability to work or perform usual activity

The relationship of an adverse event to study drug is to be assessed according to the following definitions:

1. Definitely unrelated Should be reserved for those events, which occur prior to test drug administration (e.g., washout or single-blind placebo) or for those events, which cannot be even remotely related to study participation (e.g. injury caused by a third party).
2. Unlikely There is no reasonable temporal association between the study drug and the suspected event and the event could have been produced by the subject's clinical state or other modes of therapy administered to the subject.
3. Possible The suspected adverse event may or may not follow a reasonable temporal sequence from study drug administration but seems to be the type of reaction that cannot be dismissed as unlikely. The event could have been produced or mimicked by the subject's clinical state or by other modes of therapy concomitantly administered to the subject.
4. Probable The suspected adverse event follows a reasonable temporal sequence from study drug administration, abates upon discontinuation of the drug, and cannot be reasonably explained by the known characteristics of the subject's clinical state.
5. Definitely related Should be reserved for those events, which have no uncertainty in their relationship to test drug administration: this means that a rechallenge was positive.

The outcome of each AE must be assessed according to the following classification:

1. Completely recovered The patient has fully recovered with no observable residual effects
2. Not yet completely recovered Improvement in the patient’s condition has occurred, but the patient still has some residual effects
3. Deterioration The patient’s overall condition has worsened
4. Permanent damage The AE has resulted in a permanent impairment
5. Death The patient died as a consequence of to the AE
6. Ongoing The AE has not resolved and remains the same as at onset
7. Unknown The outcome of the AE is not known because the patient did not return for follow-up (lost to follow-up)

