Dihydroartemisinin is the active metabolite of artesunate and artemether, and manufactured as an oral antimalarial drug in its own right China [13]. It has equivalent clinical efficacy to the more widely used artesunate. The mode of antimalarial action of this class of compounds is thought to involve intraparasitic Fe++ catalysed production of carbon centred free radicals.

Dihydroartemisinin is absorbed and eliminated rapidly (t1/2 circa 45 min in adult patients with uncomplicated *P. falciparum* malaria) [14]. To date no significant resistance to the artemisinin class of antimalarials has been reported and stable resistance cannot be induced in the laboratory. These drugs are safe in clinical use; there is no evidence that they produce neurotoxicity [15]. The only confirmed reports of adverse effects concern rare idiosynchratic type 1 hypersensitivity reactions [16]. There is overwhelming evidence of selected brainstem neurotoxicity from animal experiments, especially with oil-soluble artemisinin derivatives and a recent report of irreversible hearing loss after treatment with artemether-lumefantrine is of concern. However, detailed neurological examinations including pure-tone audiometry and auditory-evoked brain stem responses (ABR) failed to detect significant differences between mostly adult patients orally treated with either artesunate or artemether and age- and sex-matched controls [17]. A post-mortem comparative study of adult patients treated with either quinine or artemether for severe malaria was also negative with regard to any histopathological correlates of neuronal damages [18]. In experimental animals with early pregnancies fetal toxicity leading usually to fetal resorption occurs with high doses of the artemisinin derivatives. Clinical experience in pregnancy to date, however, has shown no cause for concern [19]. A recent WHO consensus committee concluded these drugs could be used in the second and third trimesters, but pending further information, not in the first trimester of pregnancy [20].

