#### Reporting of serious adverse events

All serious adverse events, whether or not deemed drug-related, or expected, will be reported immediately or within 24 hours (one working day), using the Serious Adverse Event Notification Form, by facsimile or email to:

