#### Dihydroartemisinin-piperaquine (Artekin)

The drug will be given once daily for 3 days.

Dosing schedule

Medications will be administered at the following times:

Day 0: hour “X”

Day 1: hour “X” + 24 hours

Day 2: hour “X” + 48 hours

Dosing table

One tablet of Artekin contains either 20 mg of dihydroartemisinin and 160 mg of piperaquine or 40 mg of dihydroartemisinin and 320 mg of piperaquine. The dosing will be based on bodyweight (assuming a linear relationship between key pharmacokinetic parameters and body weight).

| **Weight in kg** | **mg of dihydroartemisinin to be given daily** | **Dose of dihydroartemisinin as mg/kg/d** |
| --- | --- | --- |
| 4 - 6 | 10 (1/2 tablet with 20 mg) | 1.67 - 2.5 |
| 7 - 12 | 20 (1 tablet with 20 mg) | 1.67 - 2.86 |
| 13 - 23 | 40 (1 tablet with 40 mg) | 1.74 - 3.08 |
| 24 - 35 | 80 (2 tablets with 40 mg) | 2.29 - 3.33 |
| 36 - 75 | 120 (3 tablets with 40 mg) | 1.6 - 3.64 |

| **Weight in kg** | **mg of piperaquine to be given daily** | **Dose of piperaquine as mg/kg/d** |
| --- | --- | --- |
| 4 - 6 | 80 (1/2 tablet with 160 mg) | 13.36 - 20 |
| 7 - 12 | 160 (1 tablet with 160 mg) | 13.36 – 22.88 |
| 13 - 23 | 320 (1 tablet with 320 mg) | 13.92 – 24.64 |
| 24 - 35 | 640 (2 tablets with 320 mg) | 18.32 – 26.4 |
| 36 - 75 | 960 (3 tablets with 320 mg) | 12.8 – 29.12 |

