#### Safety and tolerability

The ITT population will be considered for the following analysis.

Adverse Events (AEs) will be tabulated according to degree of seriousness, time of treatment at AE onset, severity, relation to study drug, action taken, if any, and final outcome.

Vitals signs and ECG will be analysed descriptively.

ECG results will be classified as normal and abnormal. The evaluation of ECG and QT interval will be done according to the European Medicines Evaluation Agency (EMEA) directive “Point to consider: the assessment of the potential for QT interval prolongation by non-cardiovascular medicinal products”. EMEA (CPMP), London 17/12/1997 (CPMP/986/96).

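### The *probable* causality grade requires abatement on stopping the drug with no exception, so a fatal or inherently irreversible reaction with no earlier episode cannot be graded above *possible*

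*Protocol*

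**What the plan says.** Protocol 10.7.1.2 sets five grades for the relationship of an adverse event to study drug and directs that relationship be assessed by those definitions. The upper three matter here.

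- *Possible*: timing may or may not fit, and the reaction is of a type that cannot be dismissed. "The event could have been produced or mimicked by" the child's clinical state or concomitant therapy.
- *Probable*: three conditions, joined by *and*. The timing is reasonable, the event "abates upon discontinuation of the drug", and the known characteristics of the clinical state do not reasonably explain it.
- *Definitely related*: no uncertainty, and "this means that a rechallenge was positive".

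The same section lists death and permanent damage among the outcomes to be recorded. Protocol 12.3.2.2 then states: "Adverse Events (AEs) will be tabulated according to degree of seriousness, time of treatment at AE onset, severity, relation to study drug", together with action taken and final outcome.

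**The concern.** Some reactions cannot abate. A death cannot, and neither can an injury that is irreversible by its nature. The outcome list shows that the protocol expects such events to be recorded, but the causality definitions make no provision for them. As a result the outcome of an event can lower its causality grade. Of two reactions with the same timing and no alternative cause, the one that resolves may be *probable*, while the one that kills can only be *possible*.

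The background section names effects of this general kind. It says that "a recent report of irreversible hearing loss after treatment with artemether-lumefantrine is of concern", and of the artemisinin drugs that "The only confirmed reports of adverse effects concern rare idiosynchratic type 1 hypersensitivity reactions". At stake is a correct label in the table by relation to study drug. Safety is a secondary objective (9.2), and the results are intended to support registration (16).

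**Working it through.** The protocol gives no figure on this point and no arithmetic applies. The check takes one case through the definitions in 10.7.1.2.

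**Case.** A reaction that is fatal, or an injury irreversible by its nature. It has no earlier episode on a previous dose, its timing is convincing, and neither clinical state nor other therapy explains it.

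1. *Definitely related* needs a positive rechallenge. With no earlier episode there is none, so this grade is closed.
2. *Probable* needs all three conditions. Timing is met. Absence of explanation by clinical state is met. Abatement on discontinuation is not met and cannot be. The three are cumulative and carry no qualifier such as *where assessable*, so this grade is closed.
3. *Possible* has no abatement or rechallenge condition. It is the highest grade left.
4. Fit of that grade. *Possible* says that clinical state or other therapy could have produced the event. In this case the assessor has excluded both, so the description does not match. The mismatch depends on excluding both: the third condition of *probable* concerns clinical state alone, so an event meeting it could still fit *possible* through concomitant treatment.

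**Search for an exception elsewhere.** Section 10.7.1.5 refers to a further grading scale, but it grades severity, not causality. No other section gives an alternative causality rule.

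**Where the grade is used.**

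- Adverse event tables (12.3.2.2): yes, broken down by relation to study drug.
- Expedited reporting (10.7.1.4): no. "All serious adverse events, whether or not deemed drug-related, or expected, will be reported immediately".
- Stopping rule (11.1.4): no. Enrolment pauses for any serious adverse event until it is evaluated. The study stops on a classification made by the principal investigator, monitor and sponsors under GCP/ICH definitions, without reference to the five grades.
- Safety board (15.4): no. It reviews all safety data.

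**Cases outside the point.** An acute event that subsides but leaves an impairment has abated in the relevant sense. A reaction that recurs on a later dose within the course may count as a positive rechallenge. For dihydroartemisinin-piperaquine, "The drug will be given once daily for 3 days", and artemether-lumefantrine is also given in repeated doses, so such recurrence can arise.

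**The case against.** The strongest reply is that this is a legitimate strict scale. Requiring observed abatement for *probable* and rechallenge for *definitely related* is a coherent convention, and strictness has some value in an open-label trial where the assessor knows the arm. No decision turns on the difference between the two grades: the protocol nowhere defines a related event as *probable* or above, and a death graded *possible* still appears as a death in the tables of seriousness and outcome. The examples are also hypothetical. The background section cites examinations that found no significant hearing difference from controls, the flow chart schedules no hearing test, and the hypersensitivity reactions are called rare, with no fatal case mentioned.

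Most of this stands, and it sets the size of the point. It does not remove it. Strictness is defensible where abatement could have been observed and was not, because failure to improve is then evidence. It is not defensible where abatement could never be informative, because the rule then lowers the grade for a reason unrelated to causation. Investigator judgment does not cure this, since the section directs assessors to its definitions.

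A reader might infer that every event ending in permanent damage is capped at *possible*. The text does not support that: an event may subside and leave a residual impairment, and where improvement was possible, its absence is informative. A reader might also infer that *possible* can never describe an event meeting the other two conditions of *probable*. That fails too, because other therapy may remain a candidate cause.

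**Conclusion.** The point holds as a minor wording defect. Under 10.7.1.2 a fatal reaction, or an injury irreversible by its nature, with no earlier episode on a previous dose cannot be graded above *possible*, however convincing the timing and however clearly clinical state and other therapy are excluded. This rests on reading the three conditions for *probable* as cumulative, as they are written, and on the absence of any exception elsewhere in the protocol.

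Its reach is one column of a descriptive table. The number of events affected cannot be derived from the protocol and is probably very small. A reader might infer that serious drug reactions could escape reporting or fail to trigger the stopping rule. The protocol does not support that, because neither process, nor the safety board's review, depends on this scale. Efficacy conclusions are untouched.

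**What to change.** In Protocol 10.7.1.2, under *probable*:

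- After "abates upon discontinuation of the drug", add in parentheses: where this can be assessed.
- Extend the last condition so that it excludes other therapy as well as the child's clinical state.
- Add one sentence: Where abatement cannot be informative (death, or an injury irreversible by its nature), grade on timing, plausibility and absence of alternative causes.

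Leave *definitely related* unchanged, since it is reserved for events with no uncertainty. Do not make permanent damage in general the trigger, because that would take in events whose course after stopping the drug is informative.

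The change needs no new data or visits. Its downside is slightly more reliance on the judgment of investigators who know the arm in this open-label study (10.2, 11.1.2).

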#### Definition of a Serious Adverse Event

A serious adverse event (experience) (SAE) or reaction is any untoward medical occurrence that at any dose:

- Results in death;
- Is life-threatening;
- Requires hospitalization (other than for drug administration) or prolongation of existing hospitalization;
- Results in persistent or significant disability/incapacity; or
- Is a congenital anomaly/birth defect.

It also includes other important medical events (jeopardising the subject or requiring intervention to prevent one of the other outcomes listed in the definition above).

#### Reporting of serious adverse events

All serious adverse events, whether or not deemed drug-related, or expected, will be reported immediately or within 24 hours (one working day), using the Serious Adverse Event Notification Form, by facsimile or email to:

#### Reporting of adverse events

For all adverse events identified, an adverse event report form will be completed.

For each possible adverse event identified and considered as serious, a serious adverse event notification form will be completed.

The following information will be recorded for all adverse events:

1. Description of event
2. Date of event onset
3. Date event reported
4. Severity of the event
5. Relationship of the event to study medication
6. Is the event serious?
7. Initials of the person reporting the event
8. Was the event episodic or intermittent in nature?
9. Outcome of adverse event
10. Action taken
11. Date event resolved.

A severity grading scale, based on toxicity grading scales developed by the WHO and the National Institutes of Health, Division of Microbiology and Infectious Diseases, will be used to grade severity of all symptoms, physical exam findings, and haemoglobin results (see Appendix I). Any new event, or an event present at baseline that is increasing in severity, will be considered as an adverse event.

## Subject completion and withdrawal

### Subject Completion

Subjects will be described as completing the study if they satisfied all study entry criteria, have received the treatment and have attended all visits prescribed by the protocol and provided blood samples as defined for these visits.

### Subject Withdrawal from Study

During the study, the following conditions are reasons for stopping the study treatment and/or for excluding the patients from further efficacy assessments:

1. Any treatment failure (including early failures);

2. Withdrawal of informed consent;

3. Use of antimalarial drugs (or antibiotics with antimalarial activity) outside of the study protocol;

4. Persistent vomiting of study drugs on day 0 (at least twice the same dose);

5. Failure to complete the study treatment;

6. Investigator’s request for safety reasons (for example, onset of serious adverse events, necessitating study interruption);

7. Lost-to-follow up: patient cannot be located by day 28.

Patients with one or more of the conditions listed above will have to be followed-up for the safety assessment until day 42.

These reasons for premature withdrawing will be referred to Day 28 (primary evaluation time). The reasons for withdrawing between Day 29 and Day 42 will also be recorded in the study CRF.

A protocol violation occurs when an event happens that does not allow for accurate interpretation of response to treatment.

Patients meeting one of the following criteria will be considered protocol violations but will not be withdrawn from follow-up:

- violation of any eligibility criteria;
- PCR unclassifiable results;
- failure to attend a follow-up visit on Days 0-2 and patient cannot be located within 6 hours of scheduled time;
- failure to attend two consecutive follow-up visits from Day 3 to Day 28 (visits from Day 3 to 28 must take place within 24 hours of the scheduled time).

The violations listed above are not valid reasons for withdrawing the patients from follow-up (both efficacy and safety assessments). On the contrary, the investigator must do his/her best to respect the allowed time windows at every visit, even if a violation occurred at a previous visit (i.e. a previous visit did not take place or occurred outside the allowed time window).

The protocol violations listed above will not be taken into account for establishing patient inclusion in the intention-to-treat population while they will be a reason for excluding the patients from the evaluable population.

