## Study design

This study is part of a phase III, randomized, open label, two-armed study involving 5 study centres, which will enroll a total 1,500 patients (1,000 dihydroartemisinin-piperaquine; 500 artemether-lumefantrine). Each study will enroll 300 patients into the multicentre study protocol (the other study sites are in Mozambique, Burkina Faso, Uganda, Zambia). In addition, 200 additional patients will be enrolled in the KEMRI study (1) to allow an independent statistical analysis of the KEMRI study and (2) to increase the precision of the estimated chemoprophylactic effect of dihydroartemisinin-piperaquine. Patients enrolled in the KEMRI study will also be followed up for a longer period until day 84 (instead of day 42). These changes will in effect act as an amendment to the multicentre study protocol and will not interfere with the analysis of the multicentre protocol. The data from the first 300 patients (day 0 - day 42) will be fully compatible with the multicentre protocol.

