### Subject Withdrawal from Investigational Product

Subjects who withdraw from taking the investigational product should be followed-up to monitor safety up until day 28 if possible, i.e. if not previously lost to follow-up.

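### Safety follow-up ends on day 28, 42 or 84 depending on the section, so scheduled adverse-event ascertainment after day 42 depends on whether a child has been withdrawn

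*Protocol*

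**What the plan says.** The protocol gives three end days for safety observation.

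- **Day 42.** Section 10.8.2 (Subject Withdrawal from Study) applies one rule to seven reasons for stopping treatment or ending efficacy assessment, of which treatment failure is the first: "Patients with one or more of the conditions listed above will have to be followed-up for the safety assessment until day 42". It also says that reasons for withdrawing on days 29-42 are recorded, and is silent on days 43-84.
- **Day 28.** Section 10.8.4 (Subject Withdrawal from Investigational Product) says that children who stop the product should be "followed-up to monitor safety up until day 28 if possible". Not completing study treatment is also one of the seven day-42 reasons.
- **Day 84.** Section 10.2 (Study design): "Patients enrolled in the KEMRI study will also be followed up for a longer period until day 84 (instead of day 42". Table 1 schedules adverse-event recording at every visit, including days 49, 56, 63 and 84. Section 10.6 (Patient follow-up) adds that "all subjects will be seen on any day between 0 and 84 upon request".

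On ascertainment, section 10.7.1 says: "At each visit, the Investigator will ascertain the occurrence of any adverse events since the last visit". On analysis, section 12.3.2.2 (Safety and tolerability) says: "The ITT population will be considered for the following analysis". It continues: "Adverse Events (AEs) will be tabulated according to degree of seriousness, time of treatment at AE onset, severity, relation to study drug". It names no common cut-off day and no person-time denominator.

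**The concern.** Day 42 is the last visit of the multicentre protocol, so the withdrawal rule fits that trial. This site extends follow-up to day 84, and the rule appears not to have been adjusted. After day 42, scheduled visits apply to children who remain in follow-up and are not required for those already withdrawn. Because treatment failure is a withdrawal reason, the loss of observation is related to outcome and could differ between arms.

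This is mainly a data-collection rule. Since events are elicited at visits, an analysis plan cannot recover events that no scheduled visit was there to detect. If adverse events were counted over 84 days with all randomised children as the denominator, the arm with fewer withdrawals would tend to show more events at the same true rate. Safety is a stated aim of the trial, and its results are meant to support registration.

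**Working it through.** The protocol states no person-time figure, so there is none to reproduce. The check compares the sections and then sizes the possible imbalance.

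**1. Do the end days conflict?** Yes. A child who does not complete study treatment falls under both section 10.8.2 (day 42) and section 10.8.4 (day 28 if possible). Late parasitological failure (section 11.3.2.2) can occur up to day 84. For a failure on days 43-84, the day-42 limit has already passed and no other safety period is given.

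**2. What triggers the rule?** Withdrawal, including for treatment failure. Recurrence alone is not a trigger. Under section 11.3.2.2 an afebrile recurrence is a failure only if PCR shows recrudescence. Under section 11.3.2.1 febrile parasitaemia on days 4-28 is a failure with no PCR condition, so some reinfections can trigger withdrawal. The text does not settle whether other recurrences are withdrawn before the PCR result is known.

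**3. Observation time.** Let f be the proportion of an arm withdrawn by day 42, each such child then being followed to day 42. All other children are taken as followed to day 84.

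Mean scheduled safety days per child = 42f + 84(1 - f) = 84 - 42f

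Ratio (fD for dihydroartemisinin-piperaquine, fA for artemether-lumefantrine) = (84 - 42fD) / (84 - 42fA)

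The values of f are assumptions. The nearest figures in the protocol are these:

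- The 95% PCR-corrected day-28 cure ratio assumed for artemether-lumefantrine (section 10.4.2), which is 5% failure.
- About 50 breakthrough infections (section 10.5.5), or 50/250 = 20% if all are in the dihydroartemisinin-piperaquine arm. These are recrudescent or new infections over the whole follow-up.

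Neither is a withdrawal rate by day 42.

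| fD | fA | Mean days D | Mean days A | Ratio |
|---|---|---|---|---|
| 5% | 5% | 81.9 | 81.9 | 1.00 |
| 5% | 10% | 81.9 | 79.8 | 1.03 |
| 10% | 20% | 79.8 | 75.6 | 1.06 |
| 10% | 30% | 79.8 | 71.4 | 1.12 |
| 10% | 40% | 79.8 | 67.2 | 1.19 |

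**4. Effect on event counts.** If a share s of a fully observed child's events falls after day 42, the count ratio at equal true rates is (1 - s·fD) / (1 - s·fA). With s = 0.5 (a constant rate over 84 days) this equals the ratios above. Dosing is on days 0-2, and 4 of the 14 scheduled days in Table 1 come after day 42. Taking s = 4/14 = 0.286 as an alternative assumption:

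- 10% versus 30%: (1 - 0.0286) / (1 - 0.0857) = 1.06
- 5% versus 10%: (1 - 0.0143) / (1 - 0.0286) = 1.01

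**5. Effect on the share of children with at least one event.** Assume a constant rate of 1 event per 84 days in both arms. The share is f(1 - e^-0.5) + (1 - f)(1 - e^-1).

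- 5% versus 10%: 62.0% versus 60.8%, a difference of 1.2 points
- 10% versus 20%: 60.8% versus 58.4%, a difference of 2.4 points

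**The case against.** There are four arguments on the other side.

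- **The analysis detail belongs in the statistical analysis plan.** Section 12.3.2.2 does not commit to pooled counts over days 0-84, and it lists time of onset, which allows a split by period. This stands: the bias is conditional on how the tables are built. But tabulating by onset does not by itself correct the denominator after day 42, and the conflict between follow-up rules is in the protocol itself.
- **Withdrawn children can still be seen.** Section 10.6 offers visits on request to day 84, and section 10.8.2 sets a required period without forbidding later recording. This also stands: ascertainment after day 42 is reduced in withdrawn children but not absent. Visits on request are not equivalent to scheduled ones.
- **The imbalance may be small or nil.** With equal withdrawal there is none. The only comparator failure figure in the protocol is 5% at day 28, far below the 30-40% in the last rows of the table.
- **The likely direction is against the test drug.** If withdrawals are fewer on dihydroartemisinin-piperaquine, the distortion would not make it look safer than it is.

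A reader might infer something stronger: that every child who has not failed is followed to day 84, that the arm with fewer recurrences gains the observation time, and that test-arm event counts are therefore inflated by construction. The documents do not support this. The day-42 rule covers six reasons besides failure, and section 10.8.4 adds a day-28 rule. An afebrile reinfection is not a failure, and the long piperaquine half-life and chemoprophylactic effect bear mainly on reinfections. No pooled 84-day comparison is specified.

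**Conclusion.** The point holds as an inconsistency in safety follow-up with a conditional effect on the arm comparison. The protocol gives days 28, 42 and 84 in different places, two of these rules overlap for children who do not complete treatment, and failures after day 42 have no defined safety follow-up. Scheduled adverse-event ascertainment after day 42 therefore depends on withdrawal.

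The size depends on assumed withdrawal by arm and on comparing days 0-84 without person-time. The excess observation time is nil to about 6% at modest rates and 12% at 10% versus 30% withdrawn. The effect on counts is smaller if events cluster early. The primary efficacy analysis is not affected.

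**What to change.** 1. Reconcile the safety follow-up statements in sections 10.2, 10.6, 10.8.2 and 10.8.4, so that each category of child has one stated end of safety observation, including children who fail or withdraw on days 43-84. Which day applies is for the sponsor and investigators to decide.
2. Make the between-arm adverse-event comparison over one common window in which withdrawn and continuing children are both under scheduled safety follow-up. That is days 0-42 if section 10.8.2 governs. If the day-28 rule stands for some children, the window must take account of it. A common window makes scheduled time equal in both arms whatever the failure rates, apart from loss to follow-up.
3. Report later events separately, per person-time at risk, and label them as coming mainly from children not withdrawn.

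The cost is a wording change and a denominator of observed days. Visits are already recorded in the CRF and event onset dates on the adverse-event form. The downside is that late events move to a separate table.
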